### Exclusion criteria

Having breast diseases that prohibit breastfeeding; suffering from diseases whose treatment interferes with breastfeeding; mothers use of antidepressants and psychotropic drugs; mothers giving birth before the end of the fourth session of intervention; hospitalization of the baby; hospitalization of the mother; intrauterine death of the fetus.

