**Methods/design:**

A mixed methods exploratory design will be used to conduct this study in 3 phases. The first phase (qualitative): The purpose of the first phase is to understand the experience of breastfeeding mothers who had gestational diabetes, which will be done using the directed content analysis method. The purposive sampling will be used on pregnant mothers with gestational diabetes 30–34 weeks and mothers with infants (up to 6 months) with a history of gestational diabetes. The second phase include designing and implementing an educational program based on the PBT: Education will be conducted based on the needs assessment of the qualitative phase, the opinions of the focus group, and the literature review, then the breastfeeding behavior will be measured using the survey tool of “breastfeeding drop”. The third phase: Interventional quantitative phase: The sample size will be carried out by a pilot study, then a designed program as an educational intervention for teaching breastfeeding behavior based on the PBT for 30–34 weeks pregnant mothers with gestational diabetes will be implemented during 3–4 sessions and breastfeeding behavior will be evaluated after delivery.

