## Background

Gestational diabetes is a type of carbohydrate intolerance that occurs with different severity, diagnosed for the first time during pregnancy. The rate of gestational diabetes has increased along with the increase in the prevalence of diabetes risk factors such as obesity, increasing maternal age, family history of diabetes [1]. The International Diabetes Federation in 2017 estimated that 21.3 million of all live births were belong to women who had some form of hyperglycemia during pregnancy. It is estimated that 86.4% of these cases were due to gestational diabetes [2]. Research has shown that gestational diabetes is associated with multiple negative prenatal and birth outcomes, including preeclampsia, fetal macrosomia, and shoulder dystocia, followed by an increase in the rate of instrumental and cesarean delivery, and birth injuries. In addition, gestational diabetes is associated with an increased risk of long-term adverse outcomes, including type 2 diabetes in the mother in the future, increased obesity, diabetes, and cardiovascular disease in the infant [3]. One of the complications of gestational diabetes is breastfeeding failure. Despite the incomparable benefits of breast milk in providing the health of mother and infant, in mothers with gestational diabetes, the rate of breastfeeding is low. Admission to NICU, delay in lactogenesis II or incomplete information affect mothers’ breastfeeding behavior. There is no specific prescripted plan for breastfeeding mothers [4, 5].

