### Inclusion criteria

Pregnant mothers over 36 weeks or with infants in the first 6 months with a history of gestational diabetes in the last pregnancy; not having a chronic or acute disease other than gestational diabetes; willing to participate in the research and answer the questions of the questionnaire with written consent; singleton pregnancy; not having a disease whose treatment interferes with breastfeeding.

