### Sample size and sampling method

Sampling of the quantitative part of the study will be done randomly. Four health centers will be randomly selected. Two centers for the intervention group and two centers for the control group. The participants will be eligible mothers referred to the selected health centers and comprehensive health centers. After providing explanations about the study, written informed consent will be obtained. A randomized controlled method will be used regarding the purpose of the study and using the Apple system that exists in comprehensive health centers. The intervention and control groups are made up of mothers with a history of gestational diabetes covered by the mentioned centers. For blinding of the intervention, the control group will be selected from other healthcare centers and they will not receive any intervention from the research team during the study.

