### Data analysis

After collecting quantitative data, the data will be analyzed by SPSS software 21. The normality of data distribution of quantitative variables will be evaluated using the Kolmogorov–Smirnov test. Independent t-test/Mann–Whitney will be used to compare normal/abnormal quantitative variables in two groups (inter-group) and paired t-test/Wilcoxon will be used to compare normal/abnormal quantitative variables (intra-group). A significance level of 0.05 will be considered.

**Quantitative program evaluation** In a quantitative study, the impact of the educational program for mothers with gestational diabetes will be evaluated using the “breastfeeding Drop” survey tool, which is planned based on the planned theoretical constructs. With this tool, changes in “attitude, subjective norms, perceived behavior control, intention, and behavior” will be measured and compared in two intervention and control groups.

**Tool description** The “Breastfeeding Drop” survey tool, is a valid and reliable 52-question Likert-scale tool based on the theory of planned behavior and has the domains of “attitude, subjective norm and perceived behavioral control about breastfeeding”, and was designed by Janaki in 1994. This tool is also known as the “Breastfeeding Behavior Assessment Tool”. Out of 52 items of this tool, 29 are attitudinal items, 13 items are related to subjective norms and 10 items are related to perceived behavioral control. Participants will answer each item of this questionnaire on a six-point rating scale. Based on the theory of planned behavior, attitude items as beliefs related to the consequences of a certain behavior are multiplied by the score resulting from its positive or negative evaluation [29]. The validity and reliability of this tool were done in Iran in 2015 [30].

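### Excluding mothers who deliver before the fourth session can operate only in the intervention arm; the hospitalisation exclusions mainly narrow the population the result applies to

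*Protocol article*

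**What the plan says.** In the protocol article, the exclusion criteria of the quantitative phase put baseline conditions (breast disease, treatment that interferes with breastfeeding, psychotropic drugs) in one list with "mothers giving birth before the end of the fourth session of intervention; hospitalization of the baby; hospitalization of the mother", followed by fetal death.

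The quantitative section on sample size and sampling sets the arm by centre: "Two centers for the intervention group and two centers for the control group". Of the controls it says that "they will not receive any intervention from the research team during the study".

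The number of sessions and the time of entry are stated in two ways. The abstract says that the programme "for 30–34 weeks pregnant mothers with gestational diabetes will be implemented during 3–4 sessions and breastfeeding behavior will be evaluated after delivery". The inclusion criteria of the quantitative phase admit "Pregnant mothers over 36 weeks or with infants in the first 6 months with a history of gestational diabetes in the last pregnancy".

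The Background gives the reasons for poor breastfeeding in this population: "Admission to NICU, delay in lactogenesis II or incomplete information affect mothers’ breastfeeding behavior". The Specific objectives state the aim for women with gestational diabetes, without restriction to uncomplicated cases.

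The quantitative data analysis section plans an independent t-test or Mann–Whitney test between arms, with no adjustment described. The outcome instrument is a 52-item questionnaire answered on a six-point scale.

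**The concern.** A criterion that depends on how far a woman got through the programme is not an eligibility criterion. It conditions on something that happens after the arm is known, and here it refers to an event that exists in only one arm. As written, a woman in an intervention centre who delivers early leaves the study, while her counterpart in a control centre stays. The arms then differ in composition even if the programme does nothing.

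The hospitalisation clauses raise a different issue. For a woman enrolled in pregnancy, her baby's admission also comes after enrolment, and NICU admission is one of the pathways that the protocol itself gives for altered breastfeeding. Removing these mothers leaves a result for a lower-risk subset, although the stated aim covers women with gestational diabetes in general.

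Breastfeeding behaviour is evaluated after delivery. A mother excluded before then may have no outcome recorded, and no later analysis plan could bring her back.

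**Working it through.** The protocol gives no sample size, dropout rate or outcome distribution, so there is no figure to reproduce. The check is a reading of the sections side by side, followed by an illustration on assumed inputs.

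**Step 1: timing.** Centres are assigned to arms, so a woman's arm is fixed when she enrols. If she enrols pregnant, birth before the fourth session and admission of her baby can become known only later. If she enrols with an infant already born, as the inclusion criteria also allow, hospitalisation may already be known at entry. The fourth-session rule does not fit her at all: read literally, she has always given birth before that session ends.

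**Step 2: which clauses differ by arm.**

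| Clause | Intervention arm | Control arm |
|---|---|---|
| Birth before end of session four | Date defined by the programme | No sessions, and no substitute cut-off given |
| Hospitalisation of baby or mother | Applies | Applies |

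Only the first clause is asymmetric as written.

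**Step 3: size on the score scale (all inputs assumed).** Let q be the share of mothers who meet the fourth-session rule, d how much lower they score in SD units, and f the fraction of such mothers also removed from the control arm. There is no true effect, and all such mothers are removed from the intervention arm. Taking the mean of the other mothers as zero:

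- intervention mean = 0
- control mean = −d × q(1 − f) / (1 − qf)
- spurious difference = d × q(1 − f) / (1 − qf)

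With f = 0 this reduces to q × d:

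| q | d = 0.3 | d = 0.5 | d = 0.8 |
|---|---|---|---|
| 10% | 0.03 | 0.05 | 0.08 |
| 20% | 0.06 | 0.10 | 0.16 |
| 30% | 0.09 | 0.15 | 0.24 |

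With f = 1 the difference is zero for every q and d. If early births are rare, say q = 2–5%, the range with f = 0 is 0.02 × 0.3 = 0.006 to 0.05 × 0.8 = 0.04 SD.

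**Step 4: what drives q.** The spacing of sessions is not stated. With entry at 30–34 weeks, few women might deliver before a fourth session. With entry after 36 weeks, many might. The two statements of entry time therefore decide how large the problem is. The session count matters too: on a three-session course there is no fourth session, so the rule is either always met or undefined.

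**The case against.** The strongest case on the other side has four parts.

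- **The hospitalisation clauses are symmetric.** A reader might infer that all three events remove mothers differently by arm. The documents do not support that. Hospitalisation is an exclusion in both arms, and nothing suggests that education sessions change admission rates. Detection could be unequal because only the intervention arm has session contact, but that is conjecture. This part stands.
- **The prognosis of early deliverers is not documented.** A reader might infer that the fourth-session rule drops the mothers most at risk of stopping, and so certainly favours the programme. The Background links only infant admission to breastfeeding behaviour. For early delivery and maternal hospitalisation, poorer breastfeeding is a reasonable inference but is not stated. This stands: the direction of bias is probable, not established.
- **The size is speculative.** The shares and the score deficit are assumptions, and low values are plausible. A figure in percentage points of breastfeeding would also be on the wrong scale, because the programme is evaluated with a questionnaire score and no breastfeeding proportion is defined for that evaluation. This stands, and is why the illustration is in SD units.
- **The article is condensed.** It does not literally say that mothers are removed after allocation, and analysis sets may be defined elsewhere. This stands only in part. Removal follows from the timing for women enrolled in pregnancy, and the text does not say that excluded mothers stay in follow-up. The issue is a stated rule, not an omitted detail.

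The abstract's range of sessions includes four and the programme is still to be designed, so that discrepancy alone is a matter of wording. It matters here because an exclusion depends on it.

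**Conclusion.** The concern holds for the fourth-session rule. As written it is a post-allocation exclusion that can operate only in the intervention arm. It makes that arm a completer group, and the planned unadjusted comparison cannot correct for this. If early deliverers do worse, the bias favours the programme. Under the assumed inputs it is 0.03–0.24 SD for removal of 10–30% of the arm, less if early births are rare, and zero if an identical cut-off applied in both arms. The protocol supplies none of these inputs, so the figures show scale only.

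The hospitalisation exclusions are a separate and lesser matter. They do not by themselves create a difference between arms. For women enrolled in pregnancy they remove, after enrolment, a pathway that the protocol names, so the result would not describe women with gestational diabetes as a group. For mothers enrolled postpartum, hospitalisation already present at entry can be a legitimate criterion.

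**What to change.** 1. Restrict the exclusion criteria to conditions known at enrolment. Keep hospitalisation only where it is already present when a postpartum mother is enrolled.
2. Delete birth before the fourth session, and hospitalisation after enrolment, as exclusions.
3. Follow every enrolled mother with a live birth and analyse her in the arm of her centre, whatever number of sessions she attended.
4. Report session attendance and hospitalisation of mother and baby by arm. Keep a completers analysis as a sensitivity analysis only.
5. Reconcile the abstract and the exclusion criteria on the number of sessions, and the abstract and the quantitative inclusion criteria on the time of entry.

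The cost is a change of protocol wording and the follow-up of additional mothers who are already enrolled. How many depends on the entry time and session spacing that are settled. The estimated effect may be smaller, because mothers who received only part of the programme are counted.

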### Sample size and sampling method

Sampling of the quantitative part of the study will be done randomly. Four health centers will be randomly selected. Two centers for the intervention group and two centers for the control group. The participants will be eligible mothers referred to the selected health centers and comprehensive health centers. After providing explanations about the study, written informed consent will be obtained. A randomized controlled method will be used regarding the purpose of the study and using the Apple system that exists in comprehensive health centers. The intervention and control groups are made up of mothers with a history of gestational diabetes covered by the mentioned centers. For blinding of the intervention, the control group will be selected from other healthcare centers and they will not receive any intervention from the research team during the study.

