### Sample size

Since no similar article was found on breastfeeding in mothers with gestational diabetes, first a pilot study will be conducted to determine the sample size.

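### Whole health centres are assigned two per arm, but the planned between-group test treats mothers as independent, so the 0.05 level fails whenever outcomes or changes vary between centres

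*Protocol article*

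**What the plan says.** All references are to the Protocol article, quantitative phase.

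*Sample size and sampling method* fixes the allocation: "Four health centers will be randomly selected. Two centers for the intervention group and two centers for the control group". On who belongs to each arm it says: "The intervention and control groups are made up of mothers with a history of gestational diabetes covered by the mentioned centers". On the controls it adds: "the control group will be selected from other healthcare centers and they will not receive any intervention from the research team during the study". The same section calls the approach randomised: "A randomized controlled method will be used regarding the purpose of the study and using the Apple system that exists in comprehensive health centers". It describes no allocation of individual mothers within a centre.

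*Data analysis* fixes the between-group test: "Independent t-test/Mann–Whitney will be used to compare normal/abnormal quantitative variables in two groups (inter-group". For comparisons within a group, "paired t-test/Wilcoxon will be used to compare normal/abnormal quantitative variables (intra-group". The level is also fixed: "A significance level of 0.05 will be considered". The paragraph on programme evaluation in that section says that changes in the theory's constructs will be compared between the two groups. *Quantitative phase methodology* discusses pre-test–post-test designs with a control group.

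*Sample size* gives no number: "first a pilot study will be conducted to determine the sample size". No section mentions centre as a factor in the analysis, an ICC or a design effect.

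**The concern.** Every mother in a centre has the same arm, so the comparison of arms is a comparison of two centres with two other centres. Mothers at one centre share staff, catchment and usual breastfeeding support, so their scores are likely to resemble each other more than scores from different centres.

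The independent t-test takes its standard error from the spread among mothers and uses about 4m − 2 degrees of freedom for m mothers per centre. The variation that matters for the arm contrast is the variation among centres, and with two per arm only 2 degrees of freedom are available to estimate it. The Mann–Whitney test makes the same assumption of independence.

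At stake is the trial's main between-group conclusion: ordinary centre-to-centre variation could produce a significant result when the programme has no effect. A pilot-based sample size built on the same individual-level test would also make the trial too small.

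**Working it through.** The article states no sample size, power or effect size, so there is no figure of its own to reproduce. The check asks what error rate the stated test has under the stated allocation.

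**Inputs from the article.** Four centres, two per arm; arm determined by centre; individual-level t-test; level 0.05 (sidedness not stated, two-sided assumed).

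**Assumed inputs.** ICC 0.01, 0.02, 0.05 and 0.10; m = 15, 25 and 50 mothers per centre; equal centre sizes; normal outcome with total SD 1.

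**Type I error of the planned t-test.** The design effect is DE = 1 + (m − 1) × ICC. The true two-sided error is approximately 2 × [1 − Φ(1.96/√DE)].

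Example: m = 25 and ICC 0.05 give DE = 1 + 24 × 0.05 = 2.20. Then 1.96/√2.20 = 1.32, and the error is about 0.186.

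Each cell was also simulated with 20,000 trials with no programme effect. Entries are DE, then simulated error.

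| Mothers per centre | ICC 0.01 | ICC 0.02 | ICC 0.05 | ICC 0.10 |
|---|---|---|---|---|
| 15 | 1.14; 0.067 | 1.28; 0.084 | 1.70; 0.135 | 2.40; 0.210 |
| 25 | 1.24; 0.078 | 1.48; 0.109 | 2.20; 0.187 | 3.40; 0.298 |
| 50 | 1.49; 0.110 | 1.98; 0.161 | 3.45; 0.299 | 5.90; 0.427 |

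At ICC = 0 the error is about 0.05, as it should be. Repeat simulations with other random seeds differed by about 0.01 at most.

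**Comparing centre means instead.** A t-test on the four centre means has 2 × (2 − 1) = 2 degrees of freedom and a critical value of 4.30. Its simulated error stayed at 0.047–0.052 in every cell.

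**Effect of more centres, same mothers.** Assume 100 mothers per arm, a standardised difference of 0.5 and ICC 0.05. With k centres per arm, the variance of a centre mean is v = ICC + (1 − ICC)/m, the standard error is √(2v/k), and power comes from the noncentral t with 2(k − 1) degrees of freedom.

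| k per arm | m | v | Standard error | Noncentrality | df; critical t | Power |
|---|---|---|---|---|---|---|
| 2 | 50 | 0.05 + 0.95/50 = 0.0690 | 0.263 | 0.5/0.263 = 1.90 | 2; 4.30 | 0.20 |
| 4 | 25 | 0.05 + 0.95/25 = 0.0880 | 0.210 | 0.5/0.210 = 2.38 | 6; 2.45 | 0.52 |
| 5 | 20 | 0.05 + 0.95/20 = 0.0975 | 0.197 | 0.5/0.197 = 2.53 | 8; 2.31 | 0.60 |

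**The case against.** **The size rests on assumptions.** A reader might infer that the planned p-values are bound to be far too optimistic. The article does not support that without condition, because it gives neither an ICC nor a centre size. At ICC 0.01 with 15 mothers per centre the error is about 7%, which is mild. This objection stands, and the result must be given as a range.

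**Changes are to be compared.** If change scores are tested, stable differences between centres in catchment or usual support cancel. This stands in part. The ICC in the table must then be read as that of the change score, which could be smaller or larger than that of a single measurement. Centre-specific change does not cancel, and the degrees of freedom remain 2.

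**Intervals.** A reader might extend the criticism to confidence intervals. The analysis section plans none; it names tests and a level. The point is confined to p-values and type I error.

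**Individual randomisation.** A reader might take the reference to a randomised controlled method to mean that mothers are randomised individually, or take the test to presuppose this. The section describes no such allocation and takes controls from other centres. The t-test requires independent observations, not individual randomisation. The text also says that centres are chosen at random, not that the chosen centres are allocated to arms at random. If they are not, confounding with centre is a greater concern.

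**A separate analysis plan could deal with it.** None is at hand. The article does not leave the test open, however: it names the tests and the level. No analysis plan can add centres to the design.

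**Conclusion.** The concern holds in conditional form. The stated between-group test does not match the stated allocation, and nothing elsewhere in the article allows for clustering. The 0.05 level is not delivered whenever outcomes, or changes from pre-test, vary between centres. The true error is about 7–21% with 15 mothers per centre, 8–30% with 25 and 11–43% with 50, for assumed ICCs of 0.01 to 0.10, equal centre sizes and a normal outcome. These figures are for the t-test. The Mann–Whitney test was not simulated, but shares the fault.

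Correcting the test restores the error rate without rescuing the design: two centres per arm cannot separate a programme effect from a centre effect.

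**What to change.** 1. In *Data analysis*, replace the individual-level between-group test with a comparison of centre-level means, taken on the change score or the baseline-adjusted score. With four centres this has 2 degrees of freedom.
2. If four centres are kept, state that the result is preliminary and cannot separate the programme from the centres.
3. Preferably, before enrolment, amend *Sample size and sampling method* to spread the same mothers over more centres, for example 4–5 per arm, and say that the centres are allocated to arms at random.
4. In *Sample size*, multiply the pilot-based number by 1 + (m − 1) × ICC, show a range of ICCs, and allow for the few degrees of freedom.

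A mixed model with a random centre effect and a small-sample correction becomes a more reasonable option with 4–5 centres per arm. With four centres in all it is not equivalent to comparing centre means: in a check with 25–50 mothers per centre, its error reached about 7–8% at ICC 0.05–0.10. A logistic version has no basis, since the analysis section describes scale scores and names no binary outcome.

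The cost is less favourable p-values and some added site coordination. Spreading the same mothers needs no extra recruitment, but 4–5 centres per arm give power of only about 0.52–0.60 under the assumptions above. An adequately powered trial would need more than that.

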### Quantitative phase methodology

Quantitative studies are regular and systematic studies in which data are collected objectively and phenomena are studied with precise and quantitative measurements. In these studies, the obtained data are tested or described with statistical techniques [23]. Interventional studies are a type of quantitative method used to test scientific hypotheses. In experimental methods (randomized controlled clinical trials and semi-experimental designs) an intervention program is used to achieve the goals of the test, which is measured through a set of predetermined indicators. In semi-experimental designs, there is a comparison group that has the same basic characteristics as the intervention group, and after the implementation of the intervention program in the intervention group, any difference between the results of the control and intervention groups is measured [27]. Semi-experimental designs facilitate the investigation of causality in situations where complete control is not possible. Pre-test-post-test design with a comparison control group is the most common design used in research [28]. In the current mixed study, the quantitative phase will aim to determine the impact of education based on the theory of planned behavior on the breastfeeding behavior of women with gestational diabetes, which includes implementation and evaluation.

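### Taking controls from other centres is presented as blinding, which it is not, and the claimed randomised method does not say that centres are allocated to arms at random

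*Protocol article*

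**What the plan says.** All of this is in the Protocol article. The key section is Sample size and sampling method for the quantitative phase (the second section with that title).

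- **Centres.** "Four health centers will be randomly selected". The next sentence reads: "Two centers for the intervention group and two centers for the control group".
- **Mothers.** "The participants will be eligible mothers referred to the selected health centers and comprehensive health centers". Then: "After providing explanations about the study, written informed consent will be obtained".
- **Randomisation.** "A randomized controlled method will be used regarding the purpose of the study". The sentence goes on to mention an information system in the centres but does not say what that system does. The section opens by calling the sampling random.
- **Blinding.** "For blinding of the intervention, the control group will be selected from other healthcare centers". Of the control mothers it adds that "they will not receive any intervention from the research team during the study".

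Quantitative phase methodology describes randomised trials and semi-experimental designs as two kinds of experimental method, then argues for the second kind: "Semi-experimental designs facilitate the investigation of causality in situations where complete control is not possible".

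The abstract gives the intervention as 3–4 sessions. The quantitative Data analysis section names a 52-item questionnaire, answered by the participants on a six-point scale. It compares changes between the two groups using two-group and within-group tests at a 0.05 level.

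**The concern.** Two labels promise more than the described procedure delivers.

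The first is blinding. Placing controls elsewhere keeps programme material from reaching them. It does not hide from intervention mothers that they were taught, and those same mothers supply the outcome. Of the 52 items, 29 concern attitude, which the sessions aim to change and on which a taught mother may feel some answers are expected.

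The second is randomisation. Drawing centres at random helps the sample represent the population of centres. Only random allocation of those centres to arms protects the comparison, and the article does not state it.

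Consent adds to the problem. Agreeing to several sessions differs from agreeing only to questionnaires. If mothers know their centre's arm when asked, those who consent may differ between arms. The results could then be reported as blinded and randomised when the text supports neither label.

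**Working it through.** The plan gives no sample size, power or bias figure for this phase, so there is nothing to reproduce. The check is mainly a reading of the text, followed by two calculations for scale.

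**1. Who could be unaware of allocation?**

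- Intervention mothers: no, because they attend the sessions.
- Those delivering the sessions: no.
- Control mothers: possibly unaware of the programme's content, because they are at other centres and receive nothing from the research team.
- Outcome assessment: the mothers answer the items themselves, so the intervention arm's outcome comes from people who know they were taught.

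Only the control mothers might be kept in ignorance, and there is no sham or attention condition.

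**2. What is stated to be random?**

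| Step | Called random? |
|---|---|
| Sampling of the quantitative part | Yes, mechanism not described |
| Selection of four centres | Yes |
| Assignment of two centres to each arm | Not stated |
| Assignment of individual mothers | Not stated; arms are made up of whole centres |

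**3. Order of steps.** The section names the centres and arms, then the mothers referred to those centres, then explanation and consent. No timing is given, so consent after the arm is known is an inference from sentence order.

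**4. What could centre allocation achieve?** Input: 2 against 2 centres. The number of possible allocations is C(4,2) = 6. The smallest two-sided randomisation p-value is 2/6 = 0.33. Even properly random allocation of four centres cannot be relied on to balance the arms.

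**5. What would a bias do to the planned t-test?** Inputs are assumed because the documents give none: n = 30 to 100 mothers per arm, no true effect, and a bias of b SD remaining in the compared score. Clustering is ignored. The level is the plan's 0.05, taken as two-sided.

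False-positive rate = Φ(b/SE − 1.96) + Φ(−b/SE − 1.96), with SE = √(2/n) in SD units.

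Example: n = 50, b = 0.2. SE = √(2/50) = 0.2 and b/SE = 1.0. The rate is Φ(−0.96) + Φ(−2.96) = 0.170.

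| n per arm | b = 0.1 | b = 0.2 | b = 0.3 | b = 0.5 |
|---|---|---|---|---|
| 30 | 6.7% | 12.1% | 21.3% | 49.1% |
| 50 | 7.9% | 17.0% | 32.3% | 70.5% |
| 100 | 10.9% | 29.3% | 56.4% | 94.2% |

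At a fixed bias the rate rises with sample size, so enlarging the trial after the pilot would not help.

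**The case against.** A reader might infer a stronger charge than the article supports. Five points deserve a fair answer.

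- **The article does not say that mothers consent after the arm is known.** The order of the section suggests it, but no timing is stated. The point on consent must therefore stay conditional.
- **It would be too much to say that the arrangement leaves everyone aware, or that bias is wholly uncontrolled.** Control mothers may not know the programme's content. The plan also has a pre-test and compares changes, which would remove part of any stable baseline difference in attitude or intention. It would not remove biased self-report, or a difference in how more motivated mothers change.
- **The two sections do not flatly contradict each other.** Quantitative phase methodology names both kinds of design, and its sentence on semi-experimental designs is general. It leans that way without adopting the design for this trial. The label is unclear rather than contradictory.
- **The direction of any recruitment bias is not known.** Keen mothers might favour the session arm, but so might mothers worried about feeding.
- **A condensed article may leave detail to a full protocol.** Random sampling through the centres' system might limit staff choice of whom to approach, and masked procedures might be described elsewhere. Neither would correct the blinding sentence or turn random selection of centres into random allocation.

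These objections narrow the point. They do not touch the mislabelled blinding or the unstated allocation.

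**Conclusion.** The point holds in a limited form. The blinding statement is wrong as written: separate centres limit contamination, while mothers in the sessions and those delivering them know the allocation and the outcome is self-reported. The randomised label is unsupported as written, because selection of centres is called random and their allocation to arms is not. Recruitment bias is a conditional risk that depends on whether consent follows disclosure of the centre's arm.

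No size can be taken from the documents. Under the stated assumptions (bias of 0.1 to 0.5 SD, 30 to 100 mothers per arm, no true effect, clustering ignored), the nominal 5% error rate would lie between 6.7% and 94.2%. That range shows sensitivity to bias and is not an estimate for this trial. The change should be made, because it alters what the trial may conclude and costs little.

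**What to change.** In Sample size and sampling method for the quantitative phase:

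1. Replace the stated purpose of blinding with limiting contamination. State that mothers and those delivering the sessions are not blinded.
2. Allocate the four selected centres to arms by a computer-generated random sequence and call the design cluster-randomised with two centres per arm. If allocation is not random, call the design semi-experimental both there and in Quantitative phase methodology, and limit causal conclusions to match. The label depends on how centres are allocated, not on when consent is taken.
3. Where feasible, identify mothers from the centre register by the same rule in all four centres, and obtain consent and the pre-test before the centre's arm is disclosed. Once a centre's arm is disclosed it is known for every later recruit, so for mothers recruited after that, state recruitment bias as a limitation.

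The cost is a less favourable description of the design and a small scheduling burden from holding back disclosure. No new data are needed.
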